### Blinding

Researchers conducting any assessments with participants will be blind to the allocation. Should any researchers become unblind to the allocation (e.g. due to a disclosure by a school staff member), this information will be recorded and reported with the trial outcomes. Only the independent statistician, researcher coordinator and PIs will have knowledge of the school allocation. The primary analysis will be conducted by the project statistician. A fully blinded analysis is not possible because of the partially clustered data structure (intervention participants are clustered within their groups, while control group members are not).

### Timeline

Schools will be recruited in the academic year prior to the start of the intervention (i.e. for schools participating in April 2023–July 2024, we will recruit schools from September 2022–September 2023). We intend for each participating school to run a minimum of two intervention groups across two school terms and a maximum of three intervention groups across three school terms. Once schools have been recruited, consent forms will be sent to parents/carers of the participating year group cohorts asking them to indicate if they would not like their child to complete the screening measures (i.e. we will utilise an opt-out procedure). Once the deadline for returning consent forms has passed, participating adolescents will complete the SDQ, Me and My Feelings Questionnaire, and Peer Social Network nominations. We will then invite students who report SDQ total difficulties scores of 15 or higher—corresponding to the top 25% nationally, as estimated based on recent national data [51].

After the conclusion of the intervention, participants from both the intervention and control arms of the study will complete the assessment tasks measuring mental health, emotion processing and social relationship detailed in the “Outcomes” section. Once all three groups have been run within a school, we will collect follow-up measures consisting of the SDQ, M&MF and peer nomination to allow us to estimate social networks within the year group. SDQ, M&MF and peer nomination data will be collected from all students in the year group (not just those eligible to take part in the groups). Finally, 1 year following the completion of the intervention, participants from the intervention and control arms of the study will complete the full battery of assessments tasks as well as the social network measures (see Fig. 5).

**Fig. 5 Fig5:**
[figure not shown]
SPIRIT checklist outlining the timeline of the pilot intervention.⏺ = all participants are involved; ⏹ = only participants in the intervention condition are involved

## Sample size

### Sample size calculation

The present study is a cluster-randomised trial. The primary analysis model to investigate Hypothesis 1 (effectiveness of the intervention compared to a passive control) is a partially clustered mixed effects model, which takes account of the fact that participants will be clustered within intervention groups for those in the intervention arm. The analysis model also takes account of clustering within schools and within school years (see below for details on the analysis model). Power analysis for the evaluation of the intervention was conducted using published formulae for partially clustered data [96]. The two primary outcomes are the SDQ Total Difficulties Score and the Short Warwick Edinburgh Mental Wellbeing Scale (SWEMWBS).

#### Preliminary considerations

There are no trials of preventive interventions similar to ours on which we could base hypotheses about the likely size of the effect of our intervention. A meta-analysis comparing the effect of psychotherapy relative to waitlist control estimated an average standardised effect of Hedges’ *g* = 0.75 [97, 98]. Given that our intervention targets an at-risk population, rather than a clinical one, we assumed that the minimum standardised effect size we wished to detect was about half Munder et al.’s [97] estimate. We thus used a standardised effect size of δ = 0.4 for the power analysis calculations, in conjunction with considerations about clinically meaningful effect sizes.

Psychopathology will be assessed using the SDQ Total Difficulties Score. There is no consensus regarding how many point difference on the SDQ constitutes clinically meaningful change [99]. We considered that a post-intervention difference between 1 and 2 points between the intervention and control groups would be clinically meaningful. A 1-point difference corresponds to one of 20 assessed symptoms improving by 1 point; a 2-point difference corresponds to one symptom improving by 2 points, or two symptoms by 1 point each. We estimated the standard deviation of the SDQ Total Difficulties Score using the data set from the Understanding Society study (*n* = 2100) that we also used to estimate our cut-off for eligibility (top 25% of SDQ scores). In the ‘eligible’ group (who had a score of 15 or higher, *n* = 604), the mean score was 19.1, with standard deviation 3.6. Raw effect sizes of 1, 1.5 and 2 points would correspond to standardised effect sizes of about 0.28, 0.42 and 0.56. We thus considered that, by powering for a standardised effect size of 0.4, we would be able to detect a 1.5-point difference in SDQ Total Difficulties Scores post-intervention.

*Mental Wellbeing* will be assessed by the WEMWBS. There are few published data sets allowing estimation of the distribution of this scale among younger teenagers, and none for our specific at-risk population (top 25% in mental health problems). As the closest available approximation, we used data from the 2018 sweep of the Millennium Cohort Study (MCS), when cohort members were 17 years old. This was the only study we found that measured both SDQ and WEMWBS for the same participants. In contrast to our own study, the MCS used the short (7-item) version of the well-being scale, the SWEMWBS. Selecting the 25% participants with the highest SDQ total difficulties score (SDQ ≥ 15, *n* = 2473) gave us an estimate of SD = 4.7 for the SWEMWBS. We decided to assume the slightly larger SD = 5 for the calculations below, for simplicity and to err on the conservative side. It is not clear what size of points difference on the SWEMWBS is clinically meaningful or subjectively important to children, although change scores as small as either 1 or 3 points have been cited as minimally important change on the individual level [100]. Raw effect sizes of 1, 2 and 3 points would correspond to standardised effect sizes of about 0.2, 0.4 and 0.6. Since there is a high correlation between the 7-item SWEMWBS and the 14-item WEMWBS, we assume that these results will scale appropriately to the longer version of the scale, which we will use in our study.

The aim of the power analysis was to determine the number of schools that need to be recruited to give us 90% power to detect a moderate effect of the intervention (δ = 0.4) for each of the SDQ Total Difficulties Score and the WEMWBS. To correct for multiple testing of our two primary outcomes, we set alpha at 0.025 for a two-sided test. We will select larger than average schools such that each school year will have around 240 pupils or more. With 25% of pupils meeting the entry threshold, and estimating that 50% agree to take part, we considered that we are likely to recruit 30 students per school year, and thus 60 students per school. The group intervention was assumed to be delivered in groups of 10. Thus, we expect to run approximately three intervention groups per school.

We decided on 1:1 randomisation between treatment and control participants. We assumed the within-group correlation to be ICC_group_ = 0.05 and the within-year correlation to be ICC_year_ = 0.02, which are both conservative: in similar trials, intraclass correlations are often smaller (smaller ICCs would result in higher power; [96]). We also assumed a within-student autocorrelation from baseline to post-intervention measures of *r*_participant_ = 0.5. This is again conservative: the median within-participant correlation in trials is estimated to be 0.59 [101] (a higher *r*_participant_ would result in higher power). Furthermore, we assumed that the outcomes would not be related to school, which is also conservative; within-school correlation would increase the power, as each school would act as its own control. Finally, our analysis assumed up to 20% of participants lost to follow-up in both the treatment and control groups.

Under these assumptions, 540 adolescents from nine schools will need to be recruited: 270 in the intervention arm, attending 27 treatment groups, and 270 in the control arm. This would give an estimated analysis sample (after loss to follow-up) of 432. The power to detect δ = 0.4 in one outcome at the 2.5% significance level is about 92.8%. There is some room in this design for unexpected recruitment difficulties, as the power would be 90.5% if only 25 treatment groups were run and 250 controls were recruited, which would happen, for example, if two schools were able to run only two intervention groups each, instead of three.

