### Eligibility criteria

Eligible participants will include pupils who are initially in years 7–9 (ages 11–14) at the time of the first baseline assessment, with each school running the study across 2-year groups only (i.e. either years 7 and 8, or years 8 and 9). We will seek consent from parents or carers, and the participant before they are enrolled in the study. Young people at *elevated risk* of mental health problems will be invited to participate, where *elevated risk* is operationalised as having a self-reported SDQ Total Difficulties score of 15 or higher in our screening assessment. This corresponds approximately to selecting the top 25% of this age group in the UK (see ‘Outcomes,’ below for a description of this measure). This estimate is based on self-reported SDQ scores from 2100 UK adolescents aged 10–15 derived from the Understanding Society panel survey (see [51]). The 75th percentile of the SDQ Total Difficulties Score in this sample was 15. Students will be considered ineligible if they have high rates of school absence or are identified by the school as being inappropriate for the group intervention due to a high risk of harm to self or others. We will not exclude participants on the basis of neurodivergence, such as Autism and ADHD, though pre-existing diagnoses will be recorded during the study, as will participants’ use of other mental health services.

Schools will be eligible to participate if more than 30% of their pupils qualify for free school meals (Department for Education, 2022). We chose this criterion to ensure socioeconomic diversity in our sample. A record of study sites can be found at: https://www.isrctn.com/ISRCTN88585916.

Facilitators will be mental health professionals either working for schools (e.g. school counsellors) or mental health professionals that provide services within schools from external agencies (e.g. NHS Educational Mental Health Practitioners). All facilitators will attend a 2-day training course (delivered by the clinical lead, RL, and a member of the research staff, AL) to provide them with information about the intervention, opportunities to roleplay group sessions, and training on how to administer the cognitive training tasks. Facilitators will have weekly supervision with the clinical lead, RL, throughout the duration of the intervention.

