**Fig. 4 Fig4:**

Schematic of the project timeline

Procedures are also in place to account for drop-out of participants. Should any young people drop out before the intervention has begun (prior to the one-to-one meeting with the group facilitator), the next consecutive student in the list will be invited to take their place (i.e. student 31, student 32, etc.) and baseline assessments will be conducted. On the other hand, any students who ‘drop-out’ between baseline assessment and intervention will be treated as ‘intention to treat’ and therefore will be invited to take part in the follow-up assessment even if they do not participate in the ReSET group.

For the integrity of the randomisation to be preserved, it is crucial that the allocation of young people to a treatment within a given school occurs *after* all eligible children from that school (and their parents) have been screened and consented to take part. If a child or a parent knew, at the point of baseline assessment and/or at the point of making the decision whether to take part, which treatment arm they would be signing up for, then participation would not be independent of randomisation. This would risk selection effects which have the potential to cause bias in the estimation of intervention effects. As such, we will screen the entirety of the participating year groups at the first screening timepoint, and students will only be informed which group they have been allocated to only after they have completed their baseline assessment. We expect modest increases in symptomology between the screening phase and the beginning of the third set of assessments in line with population-level changes to psychopathology during adolescence (e.g. [95]). However, it is vital to the randomisation procedure that participants and their parents consent to take part in the study *prior* to when randomisation takes place, which necessitates that we screen and consent participants in the top 25% of SDQ scores at a single timepoint. We will collect SDQ data at our baseline assessment in addition to this screening questionnaire, which will allow us to adjust for changes to general psychopathology between the first screening timepoint and when the participant completes the baseline assessment.

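### The 1.5-point SDQ equivalent of 0.4 SD uses an SD truncated by the screening cut-off, so it is optimistic for the re-measured post-intervention score

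*Protocol article*

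**What the plan says.** Under Preliminary considerations, the protocol article counts a post-intervention difference of 1 to 2 SDQ points as clinically meaningful. It takes the spread of the score from a reference sample of 2,100, restricted to the 604 who scored 15 or higher, where "the mean score was 19.1, with standard deviation 3.6". It then states: "Raw effect sizes of 1, 1.5 and 2 points would correspond to standardised effect sizes of about 0.28, 0.42 and 0.56". From this it concludes that "by powering for a standardised effect size of 0.4, we would be able to detect a 1.5-point difference in SDQ Total Difficulties Scores".

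The standardised effect also has a separate source, about half of a meta-analytic estimate of 0.75: "We thus used a standardised effect size of δ = 0.4 for the power analysis calculations". For the two primary outcomes, "we set alpha at 0.025 for a two-sided test". The stated power of about 92.8% is attached to 0.4 SD.

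Eligibility means "having a self-reported SDQ Total Difficulties score of 15 or higher in our screening assessment". SDQ is measured again at baseline, after screening (Timing of randomisation), and the primary endpoint is the assessment immediately after the intervention (Primary impact outcomes).

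**The concern.** The figure of 3.6 describes the selection score itself with everything below 15 removed. A pupil who scores 16 at screening can score 9 or 12 after the intervention, so the outcome is not cut off at 15 and spreads more widely. Its SD could stay near 3.6 only if screening and outcome scores were almost perfectly correlated, yet the sample size calculation assumes a baseline-to-outcome correlation of 0.5.

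What is at stake is how δ = 0.4 is read. The protocol uses the 1.5-point figure to place the design in the middle of its clinically meaningful range. If the outcome SD is nearer 5 or 6, 0.4 SD lies at or above the top of that range.

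**Working it through.** **1. The plan's own power.** Inputs from the sample size section: 27 groups and 270 controls, 20% loss (216 analysed per arm, so 8 per group and 216/9 = 24 per school year), group ICC 0.05, year ICC 0.02, r = 0.5, two-sided α = 0.025.

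- Design factor, intervention: 1 + 7×0.05 + 23×0.02 = 1.81. Control: 1 + 23×0.02 = 1.46.
- Variance = (1 − 0.5²) × (1.81 + 1.46)/216 = 0.01135, so SE = 0.1066 SD.
- Power for 0.4 SD: 92.7% with t on 79 df (92.2% on 51 df, 93.5% by the normal approximation). Stated: 92.8%. The degrees of freedom are my assumption and matter little.

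**2. The plan's conversion.** 1.5/3.6 = 0.417 and 0.4 × 3.6 = 1.44 points. The division is right. At SD 3.6, power for 1.5 points is about 95%.

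**3. Whole-sample SD (σ), inferred because it is not given.** 604/2100 = 0.288.

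- Normal model: α = 0.560, λ = 1.186, truncated-to-full SD ratio = √(1 + αλ − λ²) = 0.509, so σ = 3.6/0.509 = 7.1.
- From the mean: σ = (19.1 − c)/(λ − α), giving 6.6 with c = 15 and 7.4 with c = 14.5.
- Skewed alternatives fitted to the same figures: beta-binomial 6.1, negative binomial 5.6.

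I use 5.5–7 as an assumption.

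**4. Post-intervention SD.** With screening-to-outcome correlation ρ in the whole population:

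SD_post = √(ρ²×3.6² + (1 − ρ²)σ²)

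If screening, baseline and outcome are equally correlated, the baseline-to-outcome correlation in the selected group is r = (ρ − ρ²k)/(1 − ρ²k), with k = 1 − (3.6/σ)².

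**5. Power for 1.5 points** (the formula in step 1, 79 df; each range runs from σ = 5.5 to σ = 7):

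| ρ | SD_post | 0.4 SD in points | implied r | power, implied r | power, r held at 0.5 |
|---|---|---|---|---|---|
| 0.5 | 5.1–6.3 | 2.0–2.5 | 0.42–0.39 | 64–43% | 68–48% |
| 0.6 | 4.9–6.0 | 2.0–2.4 | 0.50–0.46 | 72–50% | 72–53% |
| 0.7 | 4.7–5.6 | 1.9–2.2 | 0.58–0.53 | 82–61% | 77–59% |
| 0.8 | 4.4–5.1 | 1.8–2.0 | 0.68–0.62 | 94–78% | 82–68% |

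The row ρ = 0.6 is the main illustration because its implied r (0.46–0.50) is close to the plan's 0.5. Taking σ = 7.4, the largest normal-model value, would lower that row further, to about 46–49%.

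**6. Reference points.** With r = 0.5, an outcome SD of 4.0 already gives 89% for 1.5 points, just under the 90% target. For 2 points, SD 4.9–6.0 gives about 94–80%.

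**The case against.** The strongest reply is that the power calculation itself is sound. The target is 90% power for δ = 0.4, which has its own justification from the meta-analysis, and no passage attaches 92.8% to 1.5 points. That stands. A reader might infer that the stated power is wrong or that the trial must be enlarged. The documents do not support this: sample size, alpha and test rest on 0.4 SD, and the proper comparator for 1.5 points is the 95% implied by SD 3.6.

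Second, the size of the shortfall depends on two quantities that the documents do not give. That also stands. A reader might take 50–72% as established; it is one illustration. If scores are very stable (ρ = 0.8), a higher baseline-to-outcome correlation offsets much of the larger SD, and power can reach about 94%. The protocol calls its r of 0.5 conservative and cites a median of 0.59.

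Third, 2 points also counts as clinically meaningful in the protocol, and power for it stays at about 80–94% over SD 4.9–6.0. Nor does the protocol say that a null result would exclude 1.5 points.

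Finally, a reader might see the same oversight in the randomisation section: "We expect modest increases in symptomology between the screening phase and the beginning of the third set of assessments". That sentence cites a population-level developmental trend and feeds no sample size input, and the protocol plans to adjust for the re-measured baseline. It does not bear on the conversion.

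None of this rescues 3.6 as the SD of the outcome.

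**Conclusion.** The conversion uses the wrong SD. Under the selection model, any correlation below 1 gives a post-intervention SD above 3.6, so the claim that 0.4 SD corresponds to a detectable difference of 1.5 points is optimistic. The direction is secure; the amount is not. Assuming a whole-sample SD of 5.5–7 and a screening-to-outcome correlation of 0.6, 0.4 SD is about 2.0–2.4 points and power for 1.5 points is about 50–72% instead of about 95%. Across correlations of 0.5 to 0.8 the power runs from about 43% to about 94%. The fault lies in an interpretive statement about one primary outcome and in the choice of input, not in the division, the sample size or the 92.8%.

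**What to change.** Withdraw the 1.5-point statement and say that 3.6 is the SD of a score truncated by its own cut-off, so it is likely to understate the post-intervention spread. Restate the SDQ points equivalent of 0.4 SD, and the power for 1.5 points, using the SD of a re-measured SDQ in screened-in pupils. The trial's baseline SDQ, pooled over arms without regard to allocation, can serve. It is already collected, but it is a proxy for the post-intervention SD and should be described as one. Label any modelled range as an assumption.

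The cost is a text change and a less favourable stated detectable difference. Enrolment, alpha and the analysis model do not change.

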The aim of the current study is to test the impact of a novel hybrid prevention programme for young people, targeting key cognitive-emotional and social mechanisms. Specifically, we will test whether this novel hybrid intervention leads to better mental health and well-being outcomes in at-risk adolescents (highest 25% of general psychopathology risk), compared to those in a non-intervention arm. Further to this aim, we will examine whether the intervention’s impact on mental health and wellbeing is mediated by changes in emotional processing and social relationships. Our key hypotheses are as follows:(1) Our novel hybrid programme will lead to better mental health and well-being outcomes in at-risk adolescents (highest 25% of psychopathology risk), compared to those in the non-intervention arm.(2) The impact of the hybrid intervention will be mediated, in part, by changes to emotion processing and social relationships; specifically, the impact of the intervention will be mediated by:A shift in emotion perception to view fewer faces as hostile.A better ability to regulate emotions when presented with negative stimuli.Improved interoceptive ability.Improved peer acceptance and attachment with friends and parents, as well as decreased peer victimisation.

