## Outcomes

### Primary impact outcomes: general psychopathology and wellbeing

The two primary outcomes are psychopathology symptoms and mental wellbeing. Psychopathology symptoms will be assessed using the Total Difficulties Score of the Strengths and Difficulties Questionnaire (SDQ; [63]). Mental Wellbeing will be measured by the summary score of the Warwick and Edinburgh Mental Wellbeing Scale (WEMWBS; [64]). The primary endpoint will be the immediate post-intervention assessment point. Data for the primary impact outcomes will be collected prior to start of the intervention group, immediately after the intervention group has been completed, and 12-months from the first data collection timepoint (i.e. the data collected prior to the start of the intervention group). Note, these data collection timepoints are for participants allocated to both the intervention and control groups.

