### Statistical methods

#### Primary outcome analysis

The primary analyses aim to estimate the effect of the intervention on two primary outcomes: psychopathology and mental wellbeing. Psychopathology will be measured as the self-reported SDQ Total Difficulties score. The other primary outcome, mental wellbeing, will be assessed by the summary score on the Edinburgh Mental Wellbeing Scale.

The primary outcome analysis will use a partially clustered mixed effects model [102], which takes into account that participants are clustered in treatment groups in the intervention arm, but not in the control arm, via a random effect for treatment groups. The model will adjust for baseline score of the outcome measure. We will additionally control for clustering of all participants within school years via a fixed effect, and for clustering within schools via either fixed or random effects (details will be specified in the statistical analysis plan). The evidence for a treatment effect will be evaluated via a two-sided *t*-test on the coefficient of the treatment indicator variable (intervention versus control group) from the mixed effects model, using a 2.5% level of significance. Analyses will be carried out in the R software (R Core Team 2021). The primary endpoint will be post-intervention (see Fig. 4).

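### A Holm step-down would give more power than the flat 0.025 test of each primary outcome, at the same 5% family-wise error: a cheap improvement, not an error

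*Protocol article*

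**What the plan says.** The Outcomes section names the family: "The two primary outcomes are psychopathology symptoms and mental wellbeing". Under Sample size, Preliminary considerations, the protocol states the multiplicity rule: "To correct for multiple testing of our two primary outcomes, we set alpha at 0.025 for a two-sided test". The design aim in the same section is "90% power to detect a moderate effect of the intervention (δ = 0.4) for each of the SDQ Total Difficulties Score and the WEMWBS". The resulting power, for one outcome at the 2.5% level with 540 recruited and 432 analysed, is given as 92.8%. It is 90.5% if only 25 treatment groups and 250 controls are achieved.

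The Primary outcome analysis section carries the rule into the test of the treatment coefficient, "using a 2.5% level of significance". The only detail that this section hands to the statistical analysis plan is whether school enters as a fixed or a random effect. The protocol therefore states the significance rule itself. It mentions no step-down and no passing on of unused alpha.

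**The concern.** Splitting 5% equally over two tests is the Bonferroni rule. If one outcome succeeds at 0.025, its share of alpha is not needed again, and the other outcome can be tested at 0.05 with the 5% family-wise error still strongly controlled. The flat rule does not use this. The two rules differ in one situation only: one outcome has p at or below 0.025 and the other has p between 0.025 and 0.05. The flat rule then records the second outcome as not significant, and Holm records it as significant.

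This has some weight here because the first hypothesis speaks of mental health and wellbeing together: "Our novel hybrid programme will lead to better mental health and well-being outcomes in at-risk adolescents". The investigators would presumably like to be able to report on both.

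**Working it through.** **Inputs from the protocol.** Effect 0.4 SD; two-sided alpha 0.025 per outcome; 270 recruited per arm, with 27 groups of 10 in the intervention arm. "We assumed the within-group correlation to be ICC_group_ = 0.05 and the within-year correlation to be ICC_year_ = 0.02". "We also assumed a within-student autocorrelation from baseline to post-intervention measures of" 0.5. "our analysis assumed up to 20% of participants lost to follow-up in both the treatment and control groups". This leaves 216 analysed per arm, and 24 per school year (30 × 0.8). The correlation ρ between the two test statistics is not given; I assume 0 to 0.9.

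**Step 1: reproduce the stated 92.8%.** Normal approximation, baseline-adjusted:

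SE² = (1 − 0.5²) × (DE_int + DE_ctl) / 216, power = Φ(0.4/SE − 2.241)

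- Additive design effects, group size 8 after loss: DE_int = 1 + 7(0.05) + 23(0.02) = 1.81; DE_ctl = 1 + 23(0.02) = 1.46. SE² = 0.75 × 3.27/216 = 0.01135, SE = 0.1066, power = Φ(3.754 − 2.241) = 93.5%.
- Same, group size 10: DE_int = 1.91, power 92.7%.
- Multiplicative design effects, group size 8: DE_int = 1.35 × 1.46 = 1.971, power 92.3%.

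The stated figure is reproduced to within a point, so I calibrate to it: the mean of each test statistic is 2.241 + 1.461 = 3.702.

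**Step 2: exact check at ρ = 0.** Let p = 0.928 be power at 0.025 and q = Φ(3.702 − 1.960) = 0.9593 power at 0.05.

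- Flat rule, both outcomes: p² = 0.861.
- Holm, per outcome: p + (q − p)p = 0.928 + 0.0313 × 0.928 = 0.957.
- Holm, both outcomes: q² − (q − p)² = 0.9202 − 0.0010 = 0.919.

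**Step 3: other correlations.** Bivariate normal statistics, 2,000,000 draws, both true effects 0.4 SD. Power in %, flat rule → Holm:

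| ρ | Per outcome | Both | At least one |
|---|---|---|---|
| 0 | 92.8 → 95.7 | 86.2 → 91.9 | 99.5 → 99.5 |
| 0.3 | 92.8 → 95.5 | 86.9 → 92.2 | 98.7 → 98.7 |
| 0.5 | 92.8 → 95.2 | 87.6 → 92.5 | 98.0 → 98.0 |
| 0.7 | 92.8 → 95.0 | 88.7 → 93.0 | 96.9 → 96.9 |
| 0.9 | 92.8 → 94.5 | 90.4 → 93.7 | 95.2 → 95.2 |

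The ρ = 0 row agrees with Step 2 to within 0.1 point.

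**Step 4: a smaller effect on one outcome.** The protocol counts 1 SDQ point, about 0.28 SD, as clinically meaningful. With 0.28 on SDQ and 0.4 on WEMWBS (mean 3.702 × 0.7 for SDQ), SDQ power goes from about 64% to 73%. Power for both goes from 59–63% to 70–73% over ρ = 0 to 0.7. Power for at least one is again unchanged.

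**Step 5: type I error.** The flat split spends 0.025 + 0.025 = 0.05. With both nulls true, the simulated family-wise error is the same under the two rules: 0.049, 0.047 and 0.043 at ρ = 0, 0.5 and 0.7. With one null true and the other effect at 0.4, the error on the true null is 0.025 under the flat rule and 0.049, 0.046 and 0.044 under Holm, still within 0.05.

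**The case against.** The strongest reply is that nothing is broken. The flat split is prespecified, is used consistently in the power calculation and the analysis, controls family-wise error, and delivers the stated target. That stands: the protocol aims at 90% for each outcome and reaches 92.8%, or 90.5% in its reduced-recruitment case.

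A reader might infer from the wording of the first hypothesis that the trial succeeds only if both outcomes are significant, and so treat the 86–90% joint power as a shortfall against 90%. The documents do not support this. The hypothesis does not say that both tests must succeed, and no joint-power target is set. If both were required, each could be tested at 0.05 with no adjustment at all. The correction to 0.025 implies that either outcome may support a claim, and the chance of at least one success is the same under both rules.

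A reader might also take Holm to be free of any cost. It is free in sample size and family-wise error only. A 97.5% interval for the second-tested outcome may include zero while Holm rejects, a mismatch that the present rule avoids. The error for an outcome with no true effect, when the other effect is real, rises from 2.5% to just under 5%.

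Finally, the gain is modest under the design assumptions and shrinks as correlation rises. The conclusion on the second outcome changes in about 3 to 6% of trials, and the estimate and p-value would be reported either way. What survives is that, at the same family-wise level, Holm rejects everything that the flat rule rejects and sometimes more.

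**Conclusion.** This is a cheap improvement and not an error. At the stated 92.8%, with both effects at 0.4 SD and an assumed correlation of 0 to 0.9, Holm adds about 1.6 to 2.9 percentage points per outcome and about 3.3 to 5.8 points for both outcomes together. The gain is larger if one true effect is nearer to 0.28 SD. The dominance of Holm and its 5% control do not depend on any of these assumptions; only the size of the gain does. The sample size is adequate as it stands by the protocol's own criterion.

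**What to change.** In the Primary outcome analysis section, and in the statistical analysis plan if it does not already say so, add one sentence: the two primary p-values are ordered; the smaller is tested at two-sided 0.025; if it is significant, the other is tested at two-sided 0.05 (Holm); otherwise neither is declared significant.

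Leave the sample-size calculation at 0.025. Report 97.5% confidence intervals for both outcomes, and say in advance that the interval for the second-tested outcome need not agree with its Holm decision.

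The change should be made and dated before any outcome analysis. The Blinding section says that a fully blinded analysis is not possible, so a switch made after a second p-value between 0.025 and 0.05 had been seen would not be credible. There is no cost in participants, models or data collection. The price is the possible disagreement between test and interval, and the higher error for a single true null, which stays within 5%.
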